### Primary and secondary outcomes

The primary outcome measure is the DASS-21. The secondary outcome measures are the K10, SWLS and FS psychological well-being scales. Measurement will occur at baseline, mid-intervention, post intervention and at 6-month follow up.

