**Methods:**

Participants (*n* = 120) recruited via medical practitioner referral will be randomized to MiCBT or a wait-list control. Inclusion criteria are age 18–75; fluent in English and having a Kessler Psychological Distress Scale (K10) score of 20 or more. The MiCBT treatment group receive an 8-week MiCBT intervention delivered in a private psychology practice. Participants complete a suite of online self-report measures and record the amount of meditation practice undertaken each week. The control group receive usual treatment and complete the measures at the same time points. Primary outcome measures are the Depression Anxiety Stress Scale-21 (DASS-21) and K10. Analysis will use mixed-model repeated measures.

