### Aims and hypotheses

The primary aim of this study is to evaluate the effectiveness of a group delivery of MiCBT across a range of psychological disorders in a private practice setting. The secondary aim is to examine mechanisms of action underpinning MiCBT. It is hoped that the findings will also add to the body of knowledge on outcome measurement with mindfulness-based approaches, in particular the role of interoceptive, metacognitive awareness and equanimity as key mechanisms of change. Based on a preliminary pilot study [52] and experience of colleagues using MiCBT clinically, we hypothesize that the transdiagnostic application of MiCBT implemented in group format in a private psychology clinic will be more beneficial than the treatment-as-usual provided in the wait-list group. The hypotheses are that, compared to the wait-list control group, the MiCBT group will show greater decrease in clinical symptoms (self-reported levels of depression, anxiety and stress, life satisfaction and flourishing). It is further hypothesized that these improvements will be maintained over a six-month period post intervention. The study will also examine the key mechanisms of action. It is hypothesized that 1) improvements in depression, anxiety and stress scores as a function of MiCBT relative to the control group will be mediated by a) improvements in awareness (metacognitive and interoceptive awareness) and b) equanimity. Given the contribution of positive relationships with others to well-being and flourishing noted earlier, we were also interested in exploring the degree to which 2) changes in life satisfaction and flourishing scores are mediated by improvements in interpersonal skills compared to awareness and equanimity.

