#### Depression, Anxiety, and Stress Scale (DASS-21)

The DASS-21 is a 21-item version of the DASS-42 and is a self-report questionnaire designed to measure three domains: depression, anxiety and stress [54] [55, 56]. Each subscale contains 7 items, and items are rated on a four-point likert scale. Higher scores indicate more severe symptoms. The DASS-21 is reported to have high internal consistency for each of the subscales (depression, r = .88; anxiety, r = .82; stress r = .90), and the total scale (r = .93) [55, 56].

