### Sample size

The trial is powered to detect significant differences relevant to the primary outcome. A power analysis (G-power 3.1) for medium effect (Cohen’s d = .5) was conducted with power of .08, and using the conventional significance level (.05), resulting in a desired sample of 102 (51 participants in each group). Consistent with previous studies (e.g. [75]) allowing for a conservatively estimated attrition rate of 20% to follow up, a sample of 120 will be recruited. Based on the projected sample size of 102, power of 0.8, and zero, small, medium or large effect sizes conditions for the indirect effect, the mediation analyses are well-powered to detect a medium beta paths between the independent variable and the mediator and between the mediator and the dependent variable (β = .0.39) using bootstrapping and the Sobel test [76]. Data will be collected using online self-report measures with the Qualtrics platform at the four measurement points; baseline, mid-intervention, post-intervention, and 6-months follow-up.

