### Statistical analysis

Statistical analysis will be conducted using SPSS version 24 statistical software package. The dependent variables are scores on the two primary outcomes (DASS-21 and the K10), the secondary outcomes (SWLS and FS) and the other mediators (EQ, the MSES-R, the MAIA, and the NAS). The expected outcomes are that the MiCBT group will show significantly changed scores as compared to the wait-list control group, with lower scores on the DASS-21, the K10 and higher scores on the SWLS, FS, the MSES-R, the MAIA, the EQ, and the NAS.

The differential changes in the MiCBT group compared to the control group is the primary focus of the analysis. Analysis will use mixed-model repeated measures (MMRM), the method recommended for clinical trial data [77]. Evidence for the effectiveness of MiCBT will be demonstrated by a significant two-way interaction demonstrating greater change in the outcome measures in the MiCBT group from the control group pre to post intervention. Baseline to follow-up interactions for the MiCBT group will also be examined and changes compared with post intervention data. Results of the trial will be made available to referring clinicians and to participants in the form of a summarized report. Results may be published in journal articles, student thesis and conference presentations.

Intention-to-treat (ITT) analysis will be used because this approach uses all available information. Subjects with incomplete data are not discarded and missing data are not replaced with estimated values. Missing data will be examined and if found to be missing completely at random (MCAR) then the analysis will proceed without replacing missing data with estimated values. If pattern of missingness is not MCAR then multiple imputation will be applied using the strata that defined the non-random missingness.

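### The K10 is secondary in the outcomes section but primary in the abstract and the analysis section, and the sample size allows for only one primary outcome

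*Protocol article*

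**What the plan says.** Four places in the protocol article bear on which outcome is primary.

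- **Primary and secondary outcomes:** "The primary outcome measure is the DASS-21. The secondary outcome measures are the K10, SWLS and FS psychological well-being scales".
- **Abstract, Methods:** "Primary outcome measures are the Depression Anxiety Stress Scale-21 (DASS-21) and K10".
- **Statistical analysis:** "The dependent variables are scores on the two primary outcomes (DASS-21 and the K10), the secondary outcomes (SWLS and FS").
- **Sample size:** "The trial is powered to detect significant differences relevant to the primary outcome". The outcome is singular and not named, and the significance level is .05 with no split.

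The success criterion, also under Statistical analysis, is: "Evidence for the effectiveness of MiCBT will be demonstrated by a significant two-way interaction demonstrating greater change in the outcome measures" between the start and the end of treatment. It does not say whether one measure is enough or all are needed.

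The Measures section describes the DASS-21 as "designed to measure three domains: depression, anxiety and stress". It reports reliability for each of the three subscales and for the total. The hypothesis under Aims and hypotheses refers to "self-reported levels of depression, anxiety and stress, life satisfaction and flourishing". No section says which DASS-21 score is the primary variable.

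**The concern.** The K10 cannot be both primary and secondary. The outcomes section and the analysis section each list the secondary outcomes, and the lists differ by exactly the K10, so no reading reconciles them. A separate analysis plan could not simply fill this in. It would have to overrule one published section, and a reader could not tell which was meant.

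The primary outcome settles what the trial can confirm. Suppose the DASS-21 is clearly positive and the K10 is not, or the reverse. Under the outcomes section the first result is a success and the second a failure. Under the abstract and the analysis section neither result can be classified, because there is no rule for combining two primaries. The choice could then be made after the results are known, and the Blindness section says the analysis will not be blinded.

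**Working it through.** **1. What the sample size was built for.** Inputs from Sample size: d = 0.5, significance level .05, 51 per arm (102 in total). Power is printed as .08 and read here as 0.80, because 0.8 appears later in the same section.

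Normal approximation: n per arm = 2(z_alpha + z_power)² / d².

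- One-sided .05: 2(1.645 + 0.842)² / 0.25 = 49.5, so 50 per arm. The noncentral t gives 50.15, so 51 per arm = 102, with power 0.806 at 51.
- Two-sided .05: 2(1.960 + 0.842)² / 0.25 = 62.8, so 63 per arm. The noncentral t gives 64 per arm = 128.

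The printed 102 is therefore reproduced as one one-sided test at an undivided .05. It contains no allowance for a second primary.

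**2. Error rate if either of two primaries sufficed, unadjusted.** Each is tested two-sided at .05. If independent, 1 − 0.95² = 9.75%. The protocol gives no correlation between DASS-21 and K10, so a range is assumed (bivariate normal simulation, 1,000,000 draws):

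| Assumed correlation | At least one false positive, either direction | Favourable direction only |
|---|---|---|
| 0.5 | 9.1% | 4.5% |
| 0.6 | 8.8% | 4.4% |
| 0.7 | 8.3% | 4.1% |
| 0.8 | 7.8% | 3.9% |
| 0.9 | 7.0% | 3.5% |

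The nominal rates for one test are 5% and 2.5%. The right-hand column is the one that bears on a false claim of benefit.

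**3. Power if both were required.** Each test stays at .05 and type I error does not inflate. Two-sided power for one outcome at d = 0.5 and 51 per arm is 0.706. If d = 0.5 holds for both, joint power is 0.706² = 0.50 under independence, and below 0.706 for any correlation short of 1.

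**4. Power if alpha is shared.** Two-sided, d = 0.5 on both outcomes. The second row uses 48 per arm, which is 120 × 0.8 / 2.

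| Per arm | Bonferroni at .025, per endpoint | Holm, per endpoint (correlation 0.8–0.5) |
|---|---|---|
| 51 | 0.60 | 0.66–0.67 |
| 48 | 0.57 | 0.63–0.64 |

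The Bonferroni figures use the noncentral t and the Holm figures a normal-approximation simulation. Bonferroni would need 78 per arm (156 in total) for 80% power per endpoint.

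**The case against.** Much can fairly be said for the plan.

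- **The DASS-21 is primary everywhere.** Only the K10's rank varies, and the singular wording under Sample size fits the outcomes section. This stands, and it narrows the point to one measure.
- **No rule lets either outcome suffice.** A reader might infer that the team may claim effectiveness on the DASS-21 or the K10, each at the full .05. The text does not say so. The .05 appears only in the sample size calculation. The success criterion speaks of outcome measures in the plural, and the expected results are lower scores on both scales, so it can equally be read as requiring both. Multiplicity adjustment may also sit in an analysis plan that is not shown. The error inflation is therefore conditional.
- **Nothing licenses success on a subscale.** A reader might add the three DASS-21 subscales to the K10 and count four tests, with an error rate of up to 18.5% (1 − 0.95⁴). The Statistical analysis section does not mention DASS-21 subscales. It names subscales where it means them, for the MSES-R, and treats the DASS-21 as a whole. What remains is only that the primary score is unspecified, since the hypothesis lists the domains separately.
- **Two-directional rates overstate false claims of benefit.** This also stands. The favourable-direction rates are about half as large, though still above 2.5%.

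None of this removes the contradiction over the K10.

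**Conclusion.** The plan is wrong as written on one definite matter: the K10 is secondary in one section and primary in two others. The design was sized for one primary outcome. This must be reconciled because it determines what the trial can conclude.

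The consequence depends on a rule the document does not give. If either outcome sufficed unadjusted, the chance of at least one false positive would be about 7.8–9.1% two-sided, or about 3.9–4.5% in the favourable direction against 2.5%. Those ranges rest on assumed correlations of 0.8–0.5. If both were required, the cost would be power, not type I error. The documents do not support the stronger inference that familywise error necessarily exceeds 5%, or that any DASS-21 subscale could carry the claim. Which DASS-21 score is primary is a smaller but real gap.

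**What to change.** Amend the abstract and the Statistical analysis section to match Primary and secondary outcomes and Sample size. Name one primary variable in the same words in all four places: one DASS-21 score (the total, for example), with the group-by-time contrast from before treatment to week 8. List the K10 as secondary and give the remaining DASS-21 scores a stated rank. The contrast is largely in the text already, so this is a wording change; the cost is that the K10 loses primary status.

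If the sponsor wants both outcomes primary, correct the outcomes section instead. State whether one or both must be significant, state how alpha is allocated, and restate power. For d = 0.5, two-sided, at 51 per arm, the figure per endpoint is about 0.60 with Bonferroni or 0.66–0.67 with Holm, unless the sample is enlarged. The cost of this route is lower stated power or more participants.

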### Mediator hypotheses

It is hypothesized that the mediators of the clinical change will be reflected by changes in equanimity (NAS), decentering (EQ), interoceptive awareness (MAIA) and Mindfulness-based self-efficacy (MSES-R). The following mediation hypotheses will be tested: 1) improvements in the DASS-21 and K10 (clinical symptoms) at the end of MiCBT treatment will be mediated by improvements in the MSES-R (equanimity-related subscales), EQ and NAS mid-intervention; 2) improvements in clinical symptoms (DASS-21 and K10) at the six-month follow-up will be mediated by improvements in the MSES-R (equanimity-related subscales), EQ and NAS at the end of treatment. We will also explore the degree to which 3) improvements in the SWLS and FS at the six-month follow up is mediated by improvements in the MSES-R (interpersonal skills and social skills subscales) compared to MSES (equanimity subscales), EQ and MAIA measured at the end of treatment.

Measurements of ethical awareness and compassion as addressed in stage 4 of the program were not included as they would make the number of items unmanageable but could be considered in future studies and their target is relapse prevention which not the focus of this study.

### Sample size

The trial is powered to detect significant differences relevant to the primary outcome. A power analysis (G-power 3.1) for medium effect (Cohen’s d = .5) was conducted with power of .08, and using the conventional significance level (.05), resulting in a desired sample of 102 (51 participants in each group). Consistent with previous studies (e.g. [75]) allowing for a conservatively estimated attrition rate of 20% to follow up, a sample of 120 will be recruited. Based on the projected sample size of 102, power of 0.8, and zero, small, medium or large effect sizes conditions for the indirect effect, the mediation analyses are well-powered to detect a medium beta paths between the independent variable and the mediator and between the mediator and the dependent variable (β = .0.39) using bootstrapping and the Sobel test [76]. Data will be collected using online self-report measures with the Qualtrics platform at the four measurement points; baseline, mid-intervention, post-intervention, and 6-months follow-up.

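### The sample size does not deliver the stated power: 102 matches a one-sided 5% t-test that is nowhere declared, and recruiting 120 covers 15% attrition, not 20%

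*Protocol article*

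**What the plan says.** The Sample size section says the trial is powered for the primary outcome. It gives the effect size as "A power analysis (G-power 3.1) for medium effect (Cohen’s d = .5"), and says the calculation was done "with power of .08, and using the conventional significance level (.05), resulting in a desired sample of 102 (51 participants in each group"). It names neither the test nor its sidedness, and gives no correlation between repeated measurements.

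The next step inflates for loss: "allowing for a conservatively estimated attrition rate of 20% to follow up, a sample of 120 will be recruited". The mediation power statement that follows reuses the evaluable number and prints the power differently: "Based on the projected sample size of 102, power of 0.8".

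The Statistical analysis section sets the efficacy criterion: "Evidence for the effectiveness of MiCBT will be demonstrated by a significant two-way interaction", assessed from pre to post intervention in a mixed model for repeated measures (MMRM). It declares no one-sided test.

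**The concern.** The figures printed in one short paragraph do not follow from one another. Power appears with two values ten-fold apart. The evaluable number is too small for a two-sided test at the stated effect, level and power. The recruited number is too small to leave that evaluable number after the stated attrition.

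What is at stake is how the result will be read. If the trial finds no significant difference on the DASS-21, readers will judge that against a claimed 80% chance of detecting d = 0.5. If the real chance is nearer 70%, a null result says less against the intervention than the article implies. The mediation power claim also rests on 102 participants, a number not retained at the stated attrition.

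**Working it through.** **Inputs, all from the Sample size section:** d = 0.5; alpha = 0.05; power 0.80 (printed once as .08 and once as 0.8); 1:1 allocation, 51 per group; attrition 20%; 120 recruited. Sidedness is not stated, so both cases are run.

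**Is .08 a misprint?** Yes. A literal power of 0.08 would need only about 4 per group.

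**Reproducing 102.** Normal approximation: n per group = 2(z₁₋α* + z₀.₈₀)²/d², with α* = 0.05 one-sided or 0.025 two-sided.

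- One-sided: 2(1.645 + 0.842)²/0.25 = 49.5, so 50.
- Two-sided: 2(1.960 + 0.842)²/0.25 = 62.8, so 63.

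The exact t-test, which uses the noncentral t with 2n − 2 degrees of freedom and noncentrality d√(n/2), adds about one per group:

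| Test | Exact n per group | Rounded up | Total | Power at that n |
|---|---|---|---|---|
| One-sided 5% | 50.2 | 51 | **102** | 0.806 |
| Two-sided 5% | 63.8 | 64 | 128 | 0.801 |

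The one-sided test reproduces the plan's 51 per group and 102 exactly. The two-sided test does not.

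**Attrition.**

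- Retained from 120 at 20% loss: 120 × 0.80 = 96, or 48 per group. This is 6 short of 102.
- Needed to retain 102: 102/0.80 = 127.5, so 128.
- Loss that 120 can bear: 1 − 102/120 = 15%.

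Multiplying instead of dividing, 102 × 1.20 = 122.4, comes close to 120, but it is not the right inflation.

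**Power for d = 0.5, unadjusted t-test:**

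| Observed per group | Two-sided | One-sided |
|---|---|---|
| 48 (120 recruited, 20% lost) | 0.679 | 0.784 |
| 51 (stated evaluable number) | 0.706 | 0.806 |
| 60 (no loss at all) | 0.775 | 0.859 |

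At 48 per group, the effect detectable with 80% two-sided power is d = 0.58.

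**Sensitivity to the repeated-measures model.** The correlation r between baseline and week 8 is an assumption, because the article gives none. Taking d on the scale of the outcome SD, with equal variances at both times, the effective d is d/√(1 − r²) with baseline adjustment (ANCOVA) and d/√(2(1 − r)) for a change-from-baseline contrast. Two-sided power at 48 per group:

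| Assumed r | Baseline-adjusted | Change contrast |
|---|---|---|
| 0.3 | 0.720 | 0.536 |
| 0.4 | 0.753 | 0.600 |
| 0.5 | 0.799 | 0.679 |
| 0.6 | 0.858 | 0.774 |

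The change contrast reaches 80% at r of about 0.63. None of these figures allows for clustering by therapy group.

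**The case against.** The strongest reply is that the planned analysis is an MMRM, not an unadjusted t-test, and that a two-sided calculation can also arrive at 102. With baseline adjustment it does so at r of about 0.45 (128 × (1 − 0.45²) = 102.1), and with a change score at r of about 0.6 (128 × 2 × 0.4 = 102.4). This is correct, so the one-sided t-test is the most plausible origin of 102 rather than a proven one. But the article states no correlation and no baseline covariate, only Cohen's d, and the match with the one-sided t-test is exact. If a correlation was assumed, it needs to be given.

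Second, the hypotheses are directional, and a journal article may leave sidedness to the full protocol. That would make a one-sided calculation understandable. It does not help a reader who takes the conventional 5% level as two-sided, and it does not rescue the attrition step: one-sided power at 48 per group is still 0.784.

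Third, treating 96 as the analysed number is harsh. The Statistical analysis section keeps participants with incomplete data, and the 20% is attrition to follow-up, which may mean the six-month visit, whereas efficacy is judged pre to post. This stands in part. The figure of 0.68 is the unadjusted completers' power, and 0.68 to 0.78 is a fair range for that test. The top of that range assumes no loss at all and is still below 0.80.

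Finally, the attrition slip alone is small: six participants, and about two percentage points of one-sided power (0.806 to 0.784). The larger part of the problem is the gap between 102 and 128.

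**Conclusion.** The concern holds. On the article's own inputs, 102 is the two-sample t-test answer only for a one-sided 5% test, which is not declared. The two-sided answer is 128. Whatever the sidedness, 120 recruited with 20% loss leaves 96, not 102. The .08 is a misprint for 0.80.

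For an unadjusted two-sided comparison at d = 0.5, power is about 0.68 after the stated attrition and at most 0.78 with none. At the stated attrition, a true effect of that size would be missed about 32% of the time instead of 20%. These figures assume a t-test on completers and no clustering. Baseline adjustment could bring power back to about 80% at 96 observed, but only under a correlation of about 0.5 that the article does not state. A change-from-baseline contrast would need about 0.63.

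**What to change.** Rewrite the Sample size paragraph; recruitment need not change.

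1. Correct .08 to 0.80.
2. State the test on which the calculation rests and whether it is one- or two-sided.
3. Reconcile 120 with the attrition. Either keep 20% and say that 120 randomised leaves 96 with outcome data, giving two-sided power of about 68% for d = 0.5 and 80% for d = 0.58 in an unadjusted completers' comparison; or say that 120 leaves 102 at 15% attrition, with two-sided power of about 71% on the same basis.
4. If power is to be claimed from the repeated-measures analysis, state the model and the assumed correlation. With baseline as a covariate, about 80% is recovered at 96 observed if the baseline-to-week-8 correlation is at least 0.5. Do not apply that threshold to a group-by-time change contrast without a baseline covariate.
5. Align the mediation power statement, which also uses 102, with whichever retained number is chosen.

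The cost is one reworded paragraph and a less favourable stated power. For reference, keeping 80% two-sided power for the unadjusted test with 20% attrition would take 128/0.80 = 160 recruited, and keeping a declared one-sided test would take 128. Neither is needed if the paragraph states plainly what 120 can deliver.
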